### Plans to give access to the full protocol, participant level-data, and statistical code {31c}

Not applicable. There are no plans for granting public access of the full protocol, participant-level dataset, or statistical code.

## Oversight and monitoring

### Composition of the coordinating centre and trial steering committee {5d}

The Chief investigators are the trial steering committee that will provide all governance to the conduct of the study.

### Composition of the data monitoring committee, its role, and reporting structure {21a}

Not applicable. There is no data monitoring committee established for this pilot trial.

### Adverse event reporting and harms {22}

An adverse event (AE) is any event, side effect, or other untoward medical occurrences that occur in conjunction with the use of the study intervention in humans, whether or not considered to have a causal relationship to the interventions. An AE can, therefore, be any unfavourable and unintended sign (that could include a clinically significant abnormal laboratory finding), symptom, or disease temporally associated with the use of the study intervention, whether or not considered related to the intervention. Conditions recognised as being excluded from AE reporting are as follows: any event, side effect, or other medical occurrences that are anticipated because of the normal course of treatment (standard care). There are no known side effects/adverse events associated with the proposed model of care intervention [9]. Due to the nature of this intervention, there will be no reporting of AE.

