**Methods:**

We describe a protocol for a phase II, randomised controlled trial with two parallel arms and 1:1 allocation. A total of 60 patients with early-stage breast cancer will be randomised to usual, specialist-led, follow-up care (as determined by the treating surgeons, medical oncologists, and radiation oncologists) or shared follow-up care intervention (i.e. EMINENT). EMINENT is a nurse-enabled, pre-specified shared-care pathway with follow-up responsibilities divided between cancer centre specialists (i.e. surgeons and oncologists) and general practitioners. The primary outcome is health-related quality of life as measured by the Functional Assessment of Cancer Therapy—Breast Cancer. Secondary outcomes include patient experience, acceptance, and satisfaction of care; dietary, physical activity, and sedentary behaviours; financial toxicity; adherence; health resource utilisation; and adverse events.

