### Criteria for discontinuing or modifying allocated interventions {11b}

The presence of any of the following criteria constitutes cause for the withdrawal of the participant: altered mental capacity resulting in inability to provide continuing informed consent, notification from treating oncologist and/or GP that the participant is not deemed to have the capacity to consent, and recurrence or progressive disease or death.

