Patient experience of care as measured by the Picker Patient Experience 15 (PPE-15) questionnaire [30]. The PPE-15 highlights aspects of care that need improvement to monitor performance and care. It consists of 15 questions distributed to seven dimensions of care: respect, coordination, information/communication/education, physical comfort, emotional support, involvement of relatives, and transitions to community [31].Dietary behaviours, specifically usual vegetable intake and usual fruit intake, as measured by two short dietary questions from the National Nutrition Survey [32], which have been validated in the Australian population. Both questions discriminate between groups with significantly different fruit and vegetable intakes. In administering these questions, information about which foods are included as vegetables and fruits is provided and serve sizes are described.Physical activity as measured by the Active Australia Survey [33] which is designed to measure participation in leisure-time physical activity, and a single item from the International Physical Activity Questionnaire [34] will be used to measure sedentary behaviours.Financial toxicity as measured by the 11-item Comprehensive Score for financial Toxicity (COST)-Functional Assessment of Chronic Illness Therapy (FACIT) tool [35]. This tool is valid and reliable in measuring financial toxicity in patients with cancer [36].Adherence to clinical assessments including annual mammography, annual physical examination, and endocrine therapy as measured by hospital records.Emergency presentations and hospitalizations as recorded from hospital records.Satisfaction of care as measured by a 0–10 numerical analogue scale with 0 being the least satisfied and 10 being the most satisfied, supplemented with short, structured qualitative questions.Process outcomes, including completion of intervention components, as measured by completion of intervention materials such as SCPs and checklists, number and length of clinical encounters recorded from MBS data and hospital records, and barriers and facilitators to implementation as explored through semi-structured interviews with patient participants, their nominated carer, breast cancer nurses, GPs, and other healthcare providers including other nurses, and hospital- and community-based rehabilitation providers.Health resource utilisation assessing both health service use and participant out-of-pocket costs including MBS and PBS administrative data sets. These data inform participants’ utilisation of services that qualify under the MBS as well as medications dispensed under the PBS. It is planned that the economic evaluation may be reported separately from the main trial.

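### The abstract declares adverse events a secondary outcome, the harms section says none will be reported, and no collected event is designated as a harm

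*Protocol article*

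**What the plan says.** The abstract (Methods) closes its list of secondary outcomes with "financial toxicity; adherence; health resource utilisation; and adverse events".

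The harms section {22} gives a broad definition of an adverse event that does not depend on causality. It then introduces an exclusion rule ("Conditions recognised as being excluded from AE reporting are as follows"), which covers events expected in the normal course of standard treatment. Next it states that "There are no known side effects/adverse events associated with the proposed model of care intervention", and it ends: "Due to the nature of this intervention, there will be no reporting of AE".

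The list of secondary outcomes in {18a} does not name adverse events. It does include "Emergency presentations and hospitalizations as recorded from hospital records" and "Adherence to clinical assessments including annual mammography, annual physical examination, and endocrine therapy as measured by hospital records". Table 3 has no adverse-event row, but it schedules referrals back to acute care at close-out, as a process outcome.

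Under {11b}, "recurrence or progressive disease or death" is among the causes for withdrawing a participant. None of the three is listed as an outcome anywhere in the article.

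**The concern.** A reader of the abstract expects an adverse-event result by arm. A team following {22} will not produce one. Whoever writes the trial report must then either leave a declared outcome unreported or decide, after seeing the data, which of the collected events to present as adverse events. Either choice is open to criticism as selective reporting.

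There is also a gap in content. The trial is meant to inform a definitive trial of shared follow-up for patients treated with curative intent. Recurrence and death are events that the planners of that trial will want to see by arm. Here they surface only as reasons for leaving the study, and the article does not say that they will be shown by arm.

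**Working it through.** The article states no figure on this point, so there is nothing to recompute. The check is a comparison of the places that bear on it.

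1. **Is an adverse-event outcome declared?** Yes, in one place: the abstract.

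2. **Is there an instrument, source or time point for it?** No. {18a} goes through the secondary outcomes one by one without naming adverse events, and none of the Table 3 blocks (primary, secondary, participant characteristics, process) has such a row.

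3. **Is reporting ruled out?** Yes, in one place: the last sentence of {22}.

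4. **Is {22} consistent within itself?** No. A rule for what is excluded from reporting has a purpose only if something is reported. The definition also covers events whether or not they are related to the intervention, so the statement that the model has no known adverse events does not empty the category.

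5. **What safety-related data are collected under other names?**
   - Emergency presentations and hospitalisations: a listed secondary outcome in {18a}, from hospital records. Table 3 has no row of that name; they may sit under health resource utilisation, but the article does not say so.
   - Adherence to mammography, physical examination and endocrine therapy: {18a}, with a Table 3 row at close-out.
   - Referrals back to acute care: Table 3, close-out.

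   Section {20a} provides for descriptive reporting of clinical and resource outcomes and for effect-size estimates on patient and resource-use outcomes. A comparison by arm is therefore possible. None of the three is labelled a harm.

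6. **Would those measures capture recurrence and death?** Not reliably. A recurrence found at a scheduled mammogram or clinic visit need not lead to an emergency presentation or an admission. The team must still identify recurrence, progression and death in order to apply {11b}, so the information will reach the trial. What is missing is a statement that it will be tabulated. A new primary cancer is not named in {11b}, so it would need its own field.

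7. **What happens to data after such a withdrawal?** {11b} does not say. {18b} describes participants choosing how far they withdraw, which does not clearly cover a withdrawal triggered by the trial's own criteria.

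**The case against.** The strongest reply is that this is a 60-patient pilot, stated in {14} not to be a hypothesis-testing study, of a care model that {22} describes as having no known adverse events. On that view dropping general adverse-event reporting is a reasonable choice, and the only error is a stray phrase in the abstract. The phrase may simply mean the emergency presentations and hospitalisations in {18a}, and deleting or defining it would settle the matter. Much of this stands. The contradiction can be resolved in either direction, and the absence of a data monitoring committee, stated openly in {21a}, adds no error. But no section equates the abstract's phrase with the {18a} item, and deletion alone would leave recurrence and death visible only as withdrawals.

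Nor can the gap be put down to the condensing of a longer protocol. The article takes two opposite positions on the same outcome, and a fuller document would have to contradict one of them.

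A reader might infer more, in two ways that the article does not support:

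- *That the trial collects no safety comparison.* It does collect one: the three measures in step 5 can be set out by arm, and the FACT-B (physical wellbeing and breast cancer concerns) picks up part of treatment toxicity.
- *That surveillance is reduced and delayed detection is an unmeasured main risk.* In the EMINENT arm the specialist keeps 6-monthly review for 2 years post-diagnosis, and the annual GP visits are part of the same schedule. Specialist review becomes less frequent after that. Because patients may enrol up to 18 months after treatment, some could pass the 2-year point within the 12 months of follow-up. But {11a} says control follow-up is not standardised, so the article does not show that surveillance falls relative to control.

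**Conclusion.** The point holds in this form: the abstract and {22} contradict each other on whether adverse events are an outcome, {22} contradicts itself, and neither Table 3 nor {18a} provides for the outcome. One declared secondary outcome cannot be produced as the article stands. The safety-related measures that are collected are not designated as harms, and recurrence, progression and death are named only as causes of withdrawal.

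The reach is limited. The FACT-B endpoint, the feasibility outcomes and their analysis are untouched. The conclusion rests on the wording alone, with no assumption about event rates. It would weaken if the team intended the abstract's phrase to mean emergency presentations and hospitalisations; the article would then need only to say so, although recurrence and death would still lack a place in the reporting.

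**What to change.** Reconcile the abstract, {18a}, {22} and Table 3.

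- **Section {22}:** replace the last sentence with wording such as: *The harms outcome comprises emergency presentations, hospitalisations, referrals back to acute care, recurrence or new primary cancer, and death, from enrolment to 12 months. Numbers of events and of participants affected will be tabulated by randomised arm without hypothesis testing. Participants withdrawn under {11b} for these reasons are included where consent allows.* State also whether the existing exclusion for events expected under standard care applies to this list; otherwise it could remove some admissions.
- **Section {18a}:** name the same list as the harms outcome, and say what a referral back to acute care means in the control arm, where patients remain under specialist follow-up.
- **Table 3:** add one harms row at close-out.
- **Abstract:** align its wording with that list, or make the correspondence explicit in a correction or in the trial report.

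The cost is small but not nil. Emergency presentations, hospitalisations and referrals are already being collected, and recurrence and death must already be known in order to apply {11b}. A short form is needed for these and for new primaries. Recruitment was planned from 3 December 2019 to 20 November 2021, so the change is an amendment during the trial and needs ethics committee approval under {25}. With 30 patients per arm the tabulation will be descriptive only and should be presented that way.

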### Frequency and plans for auditing trial conduct {23}

There are no plans for auditing trial conduct beyond the independent research governance requirements and annual reporting to the HREC.

### Plans for communicating important protocol amendments to relevant parties (e.g. trial participants, ethical committees) {25}

All agreed protocol amendments are clearly recorded on a protocol amendment form and are signed and dated by the original protocol approving signatories. All protocol amendments will be submitted to the institutional HREC for approval before implementation. The only exception will be when the amendment is necessary to eliminate an immediate hazard to the trial participants. In this case, the necessary action will be taken first, with the relevant protocol amendment following shortly thereafter. Once HREC approval has been granted, investigators and the ANZCTR will be updated.

### Dissemination plans {31a}

It is intended that the findings from this trial will be disseminated at academic and professional conferences and via a manuscript submission to a peer-reviewed journal. Participants will be identified in such reports only in aggregate or by study identification number, gender, and age. There are no publication restrictions.

## Discussion

Despite the strong case for a shared, follow-up care model for breast cancer survivors involving cancer specialists and GPs, barriers to shared care mean that it is not routinely implemented across Australia. These include the need for coordination across multiple providers, the need for improved patient and provider knowledge about the benefits of shared care and how to implement it, insufficient or delayed communication between cancer specialists and GPs, and lack of awareness of available support such as funding models, tools, and resources [11, 12]. The current study aims to address these barriers using a Specialist Cancer Nurse to advise stakeholders of the benefits of shared care (patient and GPs), facilitate effective and timely care coordination, and act as the conduit between the specialist cancer multidisciplinary team and the GPs.

Practical issues for this trial include estimating the time required to coordinate the trial across multiple providers including engaging GPs and fidelity with the intervention components. The proposed study will provide important information on the feasibility of a definitive phase 3 trial for implementing a nurse-enabled, integrated, shared-care model involving cancer specialists and GPs for early breast cancer post-treatment follow-up. The information collected through the trial, qualitative interviews, and economic evaluations are crucial in guiding the development of such a trial.

## Trial status

The protocol published here is version 2.0 dated 24 March 2020. The trial began recruitment on 3 December 2019 and is expected to continue until 20 November 2021.

Trial registration: Australia and New Zealand Clinical Trials Registry, ACTRN12619001594112. Registered on 19 November 2019, https://www.anzctr.org.au/Trial/Registration/TrialReview.aspx?id=378690&isReview=true.

## Data Availability

There are no limitations on investigator access to the trial dataset. The datasets generated and/or analysed during the current study are not going to be made publicly available but will be made available from the corresponding author on reasonable request.

## Abbreviations

HRQoL: Health-related quality of life
GPs: General practitioners
DCIS: Ductal carcinoma in situ
REDCap: Research Electronic Data Capture
ECOG: Eastern Cooperative Oncology Group
PBS: Pharmaceutical Benefits Scheme
MBS: Medicare Benefits Schedule
SCP: Survivorship Care Plan
FACT-B: Functional Assessment of Cancer Therapy—Breast Cancer
PPE-15: Patient Experience of Care
AAS: Active Australia Survey
IPAQ: International Physical Activity Survey
COST-FACIT: Comprehensive Score for Financial Toxicity-Functional Assessment of Chronic Illness Therapy
SACQ: Self-administered Comorbidity Questionnaire
CCI: Charleston Comorbidity Index
HREC: Human Research Ethics Committee
